## Abstract

**Background:**

Lower-limb osteoarthritis (OA) causes high levels of pain and disability in adults over 45 years of age. Adopting and maintaining appropriate levels of physical activity (PA) can help patients with lower-limb OA self-manage their symptoms and reduce the likelihood of developing secondary noncommunicable diseases. However, patients with lower-limb OA are less active than people without musculoskeletal pain. This single-arm feasibility trial seeks to determine the feasibility and acceptability of a complex multicomponent physiotherapy behaviour change intervention that aims to aid patients with lower-limb OA to adopt and maintain optimal levels of PA.

**Methods:**

This trial will be conducted at one site in a National Health Service physiotherapy outpatient setting in the West Midlands of England. Up to thirty-five participants with lower-limb OA will be recruited to receive a physiotherapy intervention of six sessions that aims to optimise their PA levels during phases of behavioural change: adoption, routine formation and maintenance. The intervention is underpinned by self-determination theory (and other motivational frameworks) and seeks to foster a motivationally optimal (empowering) treatment environment and implement behaviour change techniques (BCTs) that target PA behaviours across the three phases of the intervention. Physiotherapists (*n* = 5–6) will receive training in the why and how of developing a more empowering motivational environment and the delivery of the intervention BCTs. Participants will complete patient-reported and performance-based outcome measures at baseline and 3-month (to reflect behavioural adoption) and 6-month (maintenance) post-baseline. Feasibility and acceptability will be primarily assessed through semi-structured interviews (purposively recruiting participants) and focus groups (inviting all physiotherapists and research staff). Further evaluation will include descriptive analysis of recruitment rates, loss of follow-up and intervention fidelity.

**Discussion:**

A novel complex, multicomponent theoretical physiotherapy behaviour change intervention that aims to create a more empowering motivational treatment environment to assist patients with lower-limb OA to adopt and maintain optimal PA levels has been developed. Testing the feasibility and acceptability of the intervention and its associated physiotherapist training and related trial procedures is required to determine whether a full-scale parallel group (1:1) randomised controlled trial to evaluate the interventions effectiveness in clinical practice is indicated.

**Trial registration:**

Trial register: International Standard Randomised Controlled Trial identification number: ISRCTN12002764.

Date of registration: 15 February 2022.

**Supplementary Information:**

The online version contains supplementary material available at 10.1186/s40814-023-01274-6.

## Background

Osteoarthritis (OA) is the leading cause of individual level disability for elderly adults [1] and a significant socioeconomic burden [2] which is anticipated to continue to increase [3] and engulf global healthcare systems within 10 years [4]. Lower-limb (hip and knee) OA is of primary concern, with over 300 million global cases reported, which represents an increase of over 9% from figures detailed in 1990 [5]. In the United Kingdom (UK), approximately one-in-three people over 45 years, equating to 6.6 million individuals, experience lower-limb OA symptoms [1].

Strategies to promote physical activity (PA), including planned exercises and lifestyle activities [6], are fundamental aspects of non-pharmacological interventions to help patients reduce pain and optimise function in several international OA guidelines [1, 7–9]. Physiotherapists are specialists in the assessment and management of musculoskeletal conditions and the primary healthcare provider of PA interventions within the National Health Service (NHS) in the UK [10].However, physiotherapy PA interventions help patients with lower-limb OA to moderate their clinical symptoms only over short time periods (≤ 3-month post-baseline) with symptom recurrence about 6-month post-baseline [11, 12]. Therefore, patients with lower-limb OA may seek further treatment, which places additional strain on the healthcare services. Clinical symptom regression and subsequent re-referral are likely associated with difficulties that patients with lower-limb OA experience when maintaining their prescribed PA behaviours post-discharge [13].

The Medical Research Council (MRC) [14] recommends that behaviour change theory should be utilised when developing complex interventions. Using theory enables specific behavioural determinants (e.g. self-efficacy for PA) to be targeted by the interventions’ treatment techniques [i.e. behaviour change techniques (BCTs)] [15]. Therefore, the interventions active ingredients can be modified over time, leading to potential increased clinical effectiveness on the target behaviour [15]. However, there is a lack of theoretical behaviour change interventions tested on patients with musculoskeletal pain [15].

Researchers postulate that individuals undergo several ‘phases’ of behaviour change when incorporating new behaviours into their lifestyle, with the most important phases for intervention delivery being *adoption/initiation* and *maintenance* [16]. In regard to the promotion of PA by physiotherapists, it is assumed that patients will be *adopting* PA behaviours, while receiving physiotherapy treatment and *maintenance*will be manifested and hopefully ongoing post-discharge. While it is likely that several BCTs are consistently relevant to the behaviour change process overall, others are more pertinent to either the adoption or maintenance of PA phase [17].

Randomised controlled trials (RCTs) are considered the gold standard procedure to evaluate the clinical effectiveness of an intervention. However, due to the complex processes and costs that occur when delivering and evaluating behaviour change interventions, robust scoping work prior to a definitive RCT is essential [18]. Feasibility trials are advocated to test implementation of the interventions’ procedures [19] and trial design [18], thus informing whether a full-scale RCT is warranted [20]. To date, one theoretical physiotherapy behaviour change feasibility trial has been undertaken on patients with lower-limb OA. Hurley et al. (2020) [21] evaluated the feasibility and acceptability of a complex group intervention that aimed to promote self-management behaviours in patients with musculoskeletal pain. Although the intervention was highly acceptable, eligible participants preferred to be managed individually (i.e. one to one). Low recruitment rates and delays in commencing the group intervention led to a full-scale trial being unfeasible to deliver [21]. These issues have also been highlighted in research where patients and physiotherapists did not feel they received, or were unable to deliver, effective personalised treatment within the current time slots employed in the National Health Service (NHS) [22]. Furthermore, physiotherapists most commonly treat patients with lower-limb OA 1 to 1 in clinical practice [23], and this delivery maybe more effective than group classes at aiding patients’ self-management of their levels of pain and function [24].

To address these issues, an individually delivered, complex, multicomponent theoretical behaviour change physiotherapy intervention has been developed. Briefly, the intervention and associated training programme (*Empowering Physio*™) are underpinned by self-determination theory (SDT) which focuses on the underlying reasons for individuals’ behavioural engagement [25]. The overarching aim of the intervention is to create a more motivationally empowering treatment climate to deliver BCTs that target the determinants of PA adoption and maintenance in patients with lower-limb OA.

### Aim

The trial has two primary aims:To investigate the feasibility and acceptability of a complex, multicomponent theoretical behaviour change physiotherapy intervention in the view of patients with lower-limb OA and treating physiotherapistsTo evaluate the feasibility and acceptability of trial-related procedures to participants and research-related staff

### Objectives

#### Intervention feasibility and acceptability

To determine the feasibility and acceptability of the complex and multicomponent behaviour change intervention to participants and treating physiotherapists

To determine the acceptability of the bespoke *Empowering*
*Physio* training programme to treating physiotherapists

To evaluate fidelity of intervention delivery by treating physiotherapists

#### Trial feasibility and acceptability

To measure the recruitment rates of participantsTo measure the completeness of data collection of performance-based and patient-reported outcome measures at baseline, 3- and 6-month post-baselineTo determine the feasibility and acceptability of trial-related procedures (recruitment, outcome assessment) to participants and research staffTo determine the feasibility and acceptability of utilising an accelerometer as the primary outcome in a definitive randomised controlled trialTo determine the acceptability of the patient-reported and performance-based outcome measures to participants

## Methods

### Ethics

The trial protocol has received a favourable ethical approval from the Health Research Authority via the Integrated Research Application System (IRAS number: 303710). This will ensure that the trial is conducted following best practice ethical guidelines. It will follow guidance from the Research Governance Framework for Health and Social Care and comply with the Data Protection Act 2018. Although clarification will be sought from the research team if a participant withdraws, they may do so without offering one, and their normal care will not be affected in anyway. If a person withdraws, data collected up to the point of withdrawal will be used to inform the analysis unless the participants specifically withdraw consent for this.

### Trial design

The trial will utilise a single-centre mixed-methods feasibility design including a quantitative prospective, single-arm feasibility trial with a 6-month follow-up [18, 26] and a qualitative component to provide an in-depth examination of the intervention’s feasibility and acceptability [20] in the view of participants, physiotherapists and research staff. Six months are the planned primary end point of the anticipated future definitive RCT. This is based on the generally accepted definition of behavioural maintenance in the literature [27] and large drop off in reported clinical effectiveness on PA behaviours [12] around this time point. This trial is registered with the International Standard Randomised Controlled Trial Number (ISRCTN) database (Trial ID: ISRCTN12002764) and follows Standard Protocol Items Recommendations for Interventional Trials (SPIRIT) guidelines [28]. The trial is reported in accordance with the CONSORT Statement for Pilot and Feasibility studies [29] and the COnsolidated criteria for REporting Qualitative research (COREQ) guidelines for quantitative and qualitative components respectively [30]. Figures 1 and 2 outline the flow of patients with lower-limb OA through the trial and the schedule of enrolment, intervention and assessments, respectively.

**Fig. 1 Fig1:**
[figure not shown]
Feasibility trial flow diagram

**Fig. 2 Fig2:**
[figure not shown]
Schedule of enrolment, interventions and assessments

### Trial setting and participant eligibility criteria

Patients referred for physiotherapy treatment of their hip or knee OA symptoms at the Royal Orthopaedic Hospital (ROH), Birmingham, will be invited to participate (please see Table 1 for eligibility criteria).

**Table 1 Tab1:** Eligibility criteria

Inclusion criteria
Diagnosis of unilateral or bilateral lower-limb OA based on the NICE guidelines: [1] males or females ≥ 45 years old as follows:
• Morning joint-related stiffness lasting ≤ 30 min or no morning joint-related stiffness
• Activity-related joint pain
Exclusion criteria
• A further joint-related pathology that could affect the biomechanics of the hip or knee, e.g. rheumatoid arthritis or lumbar nerve root lesion
• Previously had or awaiting knee or hip joint replacement
• Wheelchair dependent
• Unwilling/unable to give informed consent for treatment
• Unable to communicate fluently in English
• Diagnosed with a psychiatric illness (e.g. schizophrenia)
• Diagnosed with an upper motor neuron lesion, e.g. multiple sclerosis
• Unwilling/unable to attend physiotherapy sessions

All intervention procedures will take place in the ROH physiotherapy clinics or virtually via phone or ‘Attend Anywhere’, the secure NHS video call service. Ongoing PA will be undertaken by people with lower-limb OA in their own home or the community.

### Participant identification and consent

#### Feasibility trial

Potential participants will be identified from the physiotherapy waiting lists at the ROH by a member of the research team. If the patient appears to meet the eligibility criteria, they will be sent a participant information sheet (PIS) and trial consent form via post. Each potential participant will be phoned by a research nurse a minimum of 1 week later. Potential participants will be asked if they have reviewed the PIS and if they are interested in trial participation. If they report being interested, the research nurse will confirm eligibility, outline the trial and answer any outstanding questions. Consent will be taken by the research nurse during the phone call and witnessed by another ROH staff member. During the meeting, the research nurse will reiterate that participants are free to withdraw from the trial at any time, and that this will not impact on their current or future healthcare [31].

#### Multicomponent behaviour change intervention

The complex, multicomponent theoretical behaviour change intervention was developed iteratively through several interconnecting projects including the following:A systematic review that identified the most effective BCTs used in physiotherapy interventions to promote PA adherence in patients with lower-limb OA [12, 32]Semi-structured interviews with patients with lower-limb OA [17, 33]Focus groups with outpatient physiotherapistsA scoping review and mapping exercise to identify appropriate theories of behaviour change to underpin the intervention delivery and physiotherapy training

The resulting intervention, which is underpinned by self-determination theory (SDT), has the overarching aim of creating a more motivationally empowering treatment climate and to implement particular BCTs to support patients with lower-limb OA to adopt and maintain appropriate individual levels of PA. Briefly, SDT outlines three universal psychological needs (competence, relatedness and autonomy) which influence the quality of an individuals’ motivation (i.e. how self-determined that motivation is) [34]. An individual’s competence relates to their ability to effectively do the behaviour; autonomy refers to whether the engagement is voluntary and the degree of agency that an individual has with regard to the behaviour; relatedness involves feelings of being associated and optimally supported by others in regard to the behaviour [25]. SDT postulates that fulfilment of the 3 psychological needs leads to more autonomous forms of motivation and facilitates behaviour adoption and maintenance. A primarily SDT-based training programme *Empowering Coaching, * [35, 36], which has been adapted for delivery to physiotherapists (i.e. the bespoke *Empowering Physio* training), was selected to guide the training of the trial physiotherapists in regard to the motivational aspects of the intervention delivery. A brief overview of the sequential development of the intervention and associated training programme is outlined in the additonal file 2, Appendix 1 and further detail will be provided in a subsequent paper.

#### Intervention materials and associated behaviour change techniques

Support material has been developed and will be utilised to assist delivery of intervention BCTs. Participants will be given two paper-based workbooks. The first workbook targets facilitating PA adoption by encouraging the patient to reflect on their PA preferences to identify appropriate patient-centred PA goals (‘goal setting’; ‘review behaviour goals’) and includes a weekly activity planner (‘action planner’). Each participant will be given a Yamax pedometer (Tokyo, Japan) to keep that will act as a self-monitoring device (‘self-monitoring of behaviour’; ‘feedback of behaviour’) and as a thanks for partaking in the trial.

Participants will be given the second workbook in session 4. This workbook aids participants to identify necessary modifications to their physical and/or social environment (‘problem-solving’; ‘restructuring of the social environment’) to help develop a PA routine and then maintain these behaviours (‘habit formation’; ‘generalisation of the target behaviour’). A detailed list of local PA services and supports is also included [‘social support (practical)’]. Each workbook is written using needs supportive language to aid participants’ feelings of competence, autonomy and relatedness towards establishing PA as a lifestyle behaviour.

The trial-specific workbooks will be supported by the *Versus Arthritis* information booklets on knee or hip OA which outline general information on OA epidemiology, pathophysiology, management strategies (exercise and medication) and appropriate support services (‘information on health consequences of performing the behaviour’; ‘information on social and environmental consequences’). An outline of the intervention materials, their intended sequencing and associated BCTs is outlined in Table 2.

**Table 2 Tab2:** Intervention materials delivered across sessions and outline of content with associated theoretical constructs and behaviour change techniques

Session numbers	Intervention material	Intervention content	SDT constructs targeted	Associated behaviour change techniques
**1–2**	Activity Adoption Workbook	Aims of physiotherapy information on benefits of PA Exercises to identify patient-centred PA goals Activity diary	Autonomy Competence	• Goal setting (behaviour and outcome) • Problem-solving • Review behaviour goals (and/or outcome) • Action planning • Self-monitoring of behaviour (and/or outcomes of behaviour)
	Pedometer	Pedometer to self-monitor number of steps	Autonomy Competence	• Self-monitoring of behaviour (and/or outcomes of behaviour) • Feedback on behaviour (and/or outcomes)
	Versus Arthritis Book: Osteoarthritis of the Knee/Hip General Information	Epidemiology of OA Pathophysiology of OA General treatment strategies		• Information on health consequences of performing the behaviour • Information on social and environmental consequences • Modelling/demonstration of behaviour
**3–4**	Routine Formation and Maintenance Booklet	Problem-solving exercises to identify barriers and solutions to physical and social environment as needed to maintain PA Detail of local physical activity resources and support	Competence Autonomy Relatedness	• Problem-solving • Social support (practical) • Habit formation • Generalisation of a target behaviour • Restructuring of the social environment
**Any**	Theraband	Resistance band to enhance or make prescribed exercises more difficult	Autonomy Competence	• Prompts and cues • Habit formation • Adding objects to the environment

Legend: *SDT* Self-determination theory

The use of manual therapy techniques and supportive braces/walking devices will be incorporated into the intervention at the discretion of the treating physiotherapist [1]. Participants will be asked to not seek any additional treatments for their OA symptoms for the duration of the trial and to maintain their standard medications. Any co-interventions will be recorded in the assessment appointments with the research nurses.

#### Intervention delivery

Participants will attend individual intervention sessions (approximately six based on patient preference reflected in previous work related to the intervention development [33] and the standard number of physiotherapy sessions offered by the ROH) with the trained physiotherapists. Physiotherapy sessions will be conducted in person, via phone or ‘Attend Anywhere’ (based on participant preferences). Appointment frequency will depend on the participants’ availability and related PA goals and the physiotherapists’ clinical schedules. The ROH’s standard physiotherapy sessions are 45 min for an initial appointments and 30 min for a follow-up session.

#### Trial outcomes and success criteria

Once data analyses are complete, the overall trial’s success (i.e. trial-related procedures and intervention feasibility and acceptability) will be determined by evaluating the results against a priori established criteria for success (Table 3). The criteria were established by the Trial Management Group, which includes experts in musculoskeletal physiotherapy, ROH physiotherapists and researchers with expertise in trial methodology and behaviour change supported by contemporary literature in contemporary feasibility trial methodology [37]. Each criterion will be evaluated against guidance outlined by Thabane et al. (2010) [38] to determine if progression to a definitive trial is recommended. Possible outcomes include the following:Stop: A definitive trial is not feasible.Continue with modification: Modification of the protocol is required to make definitive trial feasible.Continue without modification: Modification of the protocol is not required to make definitive trial feasible but requires close monitoring.Continue without modifications: A definitive trial appears feasible.

**Table 3 Tab3:** Trial outcomes and success criteria

Aim 1: Intervention feasibility and acceptability		
**Objective**	**Method of assessment**	**Success criteria**
**Objective 1.1:** To determine the feasibility and acceptability of the complex and multicomponent behaviour change intervention to participants and treating physiotherapists (P)	• Participants: Semi-structured interviews •Physiotherapists: Focus group	**Continue without modifications**: Thematic analysis identifies that trial participants and treating physiotherapists found the intervention satisfactory (i.e. it was feasible and acceptable) in semi-structured interviews and focus groups respectively **Stop**: Thematic analysis suggests that trial participants and treating physiotherapists did not find the intervention satisfactory (i.e. it was unfeasible and/or unacceptable)
**Objective 1.2:** To determine the acceptability of the bespoke Empowering Coaching training programme (Empowering Physio) to treating physiotherapists (P)	• Focus group	**Continue without modifications**: Thematic analysis identifies that intervention physiotherapists perceived that the EC training programme developed their understanding and enactment of how to create an empowering treatment climate **Stop**: Thematic analysis suggests that intervention physiotherapists perceived that the EC training programme was insufficient to develop their understanding or enactment of how to create an empowering treatment climate
**Objective 1.3**: To evaluate fidelity of intervention delivery by treating physiotherapists (S)	• Two members of the research team will assess transcripts of one intervention session from the adoption, routine formation and maintenance phases from first and third participants for the following: 1) Intervention content by coding of BCTs 2) Treatment climate using the ISPACOT [39]	• Essential pre-specified BCTs are delivered with at least mean ‘moderate’ levels of fidelity (≥ 50%) [40] • Mean score of ≥ 4/7 on Likert scale when using ISPACOT to evaluate treatment climate [41]

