**Aim 2: Trial feasibility and acceptability**		
**Objective**	**Method of assessment**	**Success criteria**
**Objective 2.1**: To measure the recruitment rates of participants (P)	• Recording number (*n*) of participants who were sent a participant information sheet, number who agreed to participate and number recruited per month	**Continue without modification** • Target of *n* = 35 participants recruited in 9 months (approx. 4/month) • Conversion rate of ≥ 30% (number sent PIS/ number who agreed to participate) **Stop** • Target of *n* = 35 participants recruited takes > 12 months (less than 3/month) • Conversion rate of ≤ 15% (number sent PIS/ number who agreed to participate)
**Objective 2.2**: To measure the completeness of data collection of performance-based and patient-reported outcome measures at baseline, 3- and 6-month post-baseline (P)	• Record number of PROMs returned to trial team and number of participants who completed performance-based outcomes during virtual outcome assessments at each timepoint	**Continue without modification** • ≤ 80% PROM and performance-based data collected at 3-month post-baseline • ≤ 70% PROM and performance-based data collected at 6-month post-baseline **Stop** • ≤ 50% PROM and performance-based data collected at 3-month post-baseline • ≤ 50% PROM and performance-based data collected at 6-month post-baseline
**Objective 2.3**: To determine the feasibility and acceptability of trial-related procedures (recruitment, outcome assessment) to participants and ROH research staff ((P)	• Participants: Semi-structured interviews • ROH research staff: Focus groups	**Continue with modification** • Thematic analysis identifies that trial participants and ROH research staff are satisfied (i.e. feasible and acceptable) with trial procedures (e.g. recruitment, outcome assessment) in semi-structured interviews and focus groups respectively **Stop** • Thematic analysis identifies that trial participants and ROH research staff are not satisfied (i.e. they do not perceive it is feasible and/or acceptable) with trial procedures (e.g. recruitment, outcome assessment) in semi-structured interviews and focus groups respectively

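### Two of the four progression outcomes share almost the same label, Table 3 applies the labels inconsistently, and recruitment results between the favourable and Stop marks have no verdict

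*Protocol article*

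**What the plan says.** The section Trial outcomes and success criteria says that the criteria are set in advance and applied once the analyses are complete. It lists four possible outcomes. I give each a short name here:

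- Stop: "Stop: A definitive trial is not feasible".
- Modify: "Continue with modification: Modification of the protocol is required to make definitive trial feasible".
- Monitor: labelled "Continue without modification" and explained as "Modification of the protocol is not required to make definitive trial feasible but requires close monitoring".
- Go: "Continue without modifications: A definitive trial appears feasible".

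Table 3 marks five objectives as primary for progression. Each has one favourable mark and one Stop mark:

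| Objective | Favourable label, taken as defined | Favourable mark | Stop mark |
|---|---|---|---|
| 1.1 Intervention | Go (plural) | found satisfactory | "Thematic analysis suggests that trial participants and treating physiotherapists did not find the intervention satisfactory" |
| 1.2 Training | Go (plural) | developed understanding and enactment | insufficient |
| 2.1 Recruitment | Monitor (singular) | 35 "participants recruited in 9 months (approx. 4/month"); conversion ≥ 30% | more than 12 months; conversion ≤ 15% |
| 2.2 Completeness | Monitor (singular) | ≤ 80% at 3 months, ≤ 70% at 6 months (as printed) | ≤ 50% at each |
| 2.3 Trial procedures | Modify | participants and staff satisfied | not satisfied |

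After Table 3, the article adds that patient and public involvement at steering meetings will help decide what changes the intervention needs.

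**The concern.** The decision rule has two faults.

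First, the label on a good result depends on the row. A plain success in 1.1 returns Go, in 2.1 or 2.2 it returns Monitor, and in 2.3 it returns Modify. Nothing in the article explains why the best available result should carry a different verdict in each row.

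Second, two middle outcomes are defined, but no primary row says which results between its two marks belong to either. Modify says that the protocol must change, and Monitor says that it need not. If recruitment finishes in, say, month 11, the article supports neither verdict over the other. The choice would then be made with the data in view, which defeats the purpose of setting criteria in advance.

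**Working it through.** **1. The plan's own rates reproduce.** From Table 3, Objective 2.1: 35/9 = 3.89 per month (stated as about 4) and 35/12 = 2.92 per month (stated as less than 3).

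**2. Recruitment time.** The favourable mark is 9 months and Stop is more than 12 months. Finishing after more than 9 and up to 12 months, or about 2.9 to 3.9 per month, meets neither.

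**3. Conversion.** Table 3 prints the ratio as sheets sent over number agreeing. That ratio cannot fall below 100%, so I read it as agreed over sent. The article gives no number of sheets. I assume 35/0.30 = 116.7, so 117. The Sample size section's three eligible patients a week over 39 weeks (9 × 52/12) also gives 3 × 39 = 117.
- Stop: 0.15 × 117 = 17.55, so 17 or fewer agree.
- Favourable: 0.30 × 117 = 35.1, so 36 or more agree.
- No verdict: 18 to 35 agree.

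With X ~ Binomial(117, p), P(18 ≤ X ≤ 35) is:

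| True rate p | P(between the marks) |
|---|---|
| 20% | 0.91 |
| 25% | 0.90 |
| 30% | 0.54 |
| one in three (Sample size section) | 0.25 |

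All rates except one in three are my assumptions.

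**4. Completeness as printed, n = 35.** Stop is 0 to 17 (17/35 = 48.6%; 18/35 = 51.4%).
- At 3 months, ≤ 80% covers 0 to 28, since 28/35 = 80%. Counts of 0 to 17 meet both marks, 18 to 28 meet the favourable mark, and 29 to 35 meet neither.
- At 6 months, ≤ 70% covers 0 to 24 (24/35 = 68.6%). Counts of 0 to 17 meet both marks, 18 to 24 meet the favourable mark, and 25 to 35 meet neither.

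As printed, there is no middle gap. The results with no verdict are the best ones.

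**5. Completeness with the signs read as ≥.** The favourable range becomes 28 to 35 at 3 months and 25 to 35 at 6 months. That leaves 18 to 27 and 18 to 24 without a verdict. With X ~ Binomial(35, p):

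| Assumed true completeness | 3 months, P(18 ≤ X ≤ 27) | 6 months, P(18 ≤ X ≤ 24) |
|---|---|---|
| 60% | 0.88 | 0.77 |
| 70% | 0.86 | 0.48 |
| 75% | 0.68 | 0.24 |
| 80% | 0.40 | 0.08 |
| 90% | 0.02 | 0.00 |

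**The case against.** The best defence is that these are editing slips. The final s is probably typographical, as are the ≤ signs in 2.2, the inverted conversion ratio and the label in 2.3, and a sensible steering group would read through them. I accept that as the likely origin. It does not settle the rule, because the two near-identical labels are given different meanings and the middle band is unassigned even after every slip is corrected. The consultation described after Table 3 does not fill the gap either, since it concerns changes to the intervention and not recruitment or completeness.

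Several stronger readings are tempting, and the article does not support them:

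- A reader might infer that Table 3 uses only two of the four outcomes. That is true of each primary row, not of the table. Objective 2.3 uses Modify, and if singular and plural are kept apart all four labels appear.
- A reader might infer that the authors meant recruitment and completeness never to return Go. The labels say so literally, but nothing suggests that it was intended.
- A reader might call the middle band the likely result. That depends on the true rate. At the protocol's own one in three, the chance for conversion is 0.25.
- A reader might say that 50–80% completeness has no verdict. As printed it has one; the gap appears only once ≤ is corrected to ≥.
- Objective 1.1 words both marks for participants and physiotherapists jointly, so a split between them is not literally covered. That is a qualitative judgement, and its results go to the Trial Steering Group for challenge. I do not rest the point on it.

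**Conclusion.** The point holds in this form. The progression labels collide and are applied inconsistently across the five primary rows. Read as defined, full success in 2.1 returns Monitor, and a satisfied result in 2.3 returns Modify. In 2.1, recruitment taking more than 9 and up to 12 months, or conversion above 15% and below 30%, has no verdict, and the two candidates are opposite on whether the protocol must change. In 2.2 the same gap is conditional on correcting the signs; uncorrected, that row has the different fault of overlapping marks at the bottom and none at the top.

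The middle band is a substantial possibility rather than a certainty. For conversion the chance runs from 0.25 to 0.91 over true rates from one in three down to 20%. For 3-month completeness it runs from 0.40 to 0.86 over 80% down to 70%. These figures assume a fixed 117 sheets, 35 participants, independent responses, conversion read as agreed over sent, and ≥ in 2.2. The label inconsistency and the recruitment-time gap need none of these assumptions. The change should be made, because these criteria decide whether a definitive trial goes ahead.

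**What to change.** In Trial outcomes and success criteria and Table 3:

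1. Rename the third outcome *Continue without modification, with close monitoring*, so that it cannot be confused with the fourth.
2. Use the fourth outcome's label for the favourable mark in every primary row, including 2.1, 2.2 and 2.3.
3. Change the favourable signs in 2.2 to ≥ 80% at 3 months and ≥ 70% at 6 months, and write the conversion ratio in 2.1 as number agreeing over number sent a sheet.
4. State that results between the favourable and Stop marks are *Continue with modification*. Alternatively, the Trial Management Group can set its own split between monitoring and modification. The article gives no basis for a particular cut-off, so I suggest none.

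The wording should be fixed before results are compared with the criteria. It needs no new data or analysis. The cost is that the group commits in advance to a verdict for the middle band and gives up discretion there.
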